**Figure 9 figure9:**
[figure not shown]
Participants will respond to an end-of-day ecological momentary assessment to confirm whether they performed exercises (aerobic, strength, or both).

#### Personalized PA Threshold Identification

A multifaceted approach of using self-reported PA data with sensor data from the smartwatch during the baseline period will help identify personalized PA thresholds. These personalized PA thresholds are then used by the JITAI to determine whether minutes of moderate-intensity PA per day for each participant have been achieved each day for the rest of the study period. Baseline PA data are quantified using a motion summary measure that is computationally feasible on the smartwatch for real-time computation. Area under the curve (AUC) values obtained from high-pass–filtered triaxial accelerometer signals are summed each minute to obtain a single motion measure per minute, which is then further summed throughout the day. The AUC values provide a quantitative and cumulative measure of PA over time because they integrate the intensity of motion activity over time. The choice of a relatively simple measure of PA intensity is due to its low computational demands on the central processing unit, causing a reduced impact on the battery life of the smartwatch. In addition, self-reported PA data are collected through the Physical Activity Recall Assessment for people with SCI, which provides subjective insights from the participants [46]. After the baseline data collection, we will meticulously compare the self-reported PA data with AUC data to determine a new threshold value for each participant (Figure 10) to gain a more comprehensive understanding of their actual PA levels and intensity. The rationale for this process is due to various functional deficits resulting from complete or incomplete SCI at different neurological levels (cervical, thoracic, lumbar, and sacral) [47]. These functional deficits, in turn, lead to large biomechanical variations of upper extremity use during exercise and mobility. Moreover, developing person-specific models that are trained to recognize the types of activities each person with SCI can perform would be burdensome. Our approach of using movement data from a wrist-worn smartwatch allows us to generalize the intervention to persons with SCI without requiring them to come to a laboratory for extensive measurements.

**Figure 10 figure10:**
[figure not shown]
Flowchart to identify a personalized physical activity (PA) threshold. The new threshold value will allow us to calculate minutes of moderate-intensity PA per day for each participant. AUC: area under the curve; PARA-SCI: Physical Activity Recall Assessment for people with spinal cord injury.

### Sample Size Determination

Sample size calculation for the primary aim (a 2-arm randomized controlled trial) indicated that 82 participants are needed per group to detect at least a standardized mean difference of 0.44 [48] (considered small to moderate) in the primary outcome, with 80% power (assuming a 2-sided test with an α level of .05). On the basis of prior research [49,50] and our pilot study [24], we anticipate a 20% dropout rate. Thus, we plan to recruit a total of 196 participants with SCI (98 participants per group). In addition, power analysis for the secondary aim (an MRT) based on 2 randomizations per day indicated that a sample size of 69 is needed to detect a difference between JITAI message and no message on the proximal PA achieved for the WI+JITAI arm [30,51]. We assumed an average proximal treatment effect for message versus no message of 0.10 (considered small) that starts with 0.12 (ie, a small effect) and decreases linearly for the 16 weeks, an α level of .05, and 80% power [30]. We will have sufficient power for the MRT given we plan to recruit 98 individuals for the WI+JITAI arm to ensure that the primary aim is powered.

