**Methods:**

Individuals with SCI (N=196) will be randomized to a WI arm or a WI+JITAI arm. Within the WI+JITAI arm, a microrandomized trial will be used to randomize participants several times a day to different tailored feedback and PA recommendations. Participants will take part in the 24-week study from their home environment in the community. The study has three phases: (1) baseline, (2) WI program with or without JITAI, and (3) PA sustainability. Participants will provide survey-based information at the initial meeting and at the end of weeks 2, 8, 16, and 24. Participants will be asked to wear a smartwatch every day for ≥12 hours for the duration of the study.

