#### Primary Aim Analysis

We hypothesize that the integration of WI+JITAI will produce significantly higher PA levels over 14 weeks than the standard WI alone. Exploratory outcomes include long-term PA (measured via sensors and self-report) over 24 weeks (approximately 6 months). To test our hypothesis, we will fit a mixed-effects model in which the group indicator variable is a predictor, and the outcomes are the PA measurements at 2, 8, and 16 weeks. We will include an interaction with time in the model because we hypothesize that although PA levels may increase in both groups, they will increase more in the WI+JITAI group. We will also include a random intercept and slope for time. To evaluate long-term PA, we will include the PA levels at 24 weeks in the model.

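### After the plan's own 20% dropout, 98 per group leaves about 78, not the 82 it says it needs for 80% power

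*Protocol article*

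**What the plan says.** The calculation is in the protocol article, Methods, Sample Size Determination. Its steps, in order, are:

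- The requirement for the primary two-arm comparison: "82 participants are needed per group to detect at least a standardized mean difference of 0.44", "with 80% power (assuming a 2-sided test with an α level of .05").
- The expected loss, attributed to prior research and the team's pilot study: "we anticipate a 20% dropout rate".
- The conclusion: "Thus, we plan to recruit a total of 196 participants with SCI (98 participants per group").

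The last step opens as a consequence of the two before it, so 98 is presented as 82 adjusted for 20% dropout. No inflation formula is given. The Abstract carries the same total: "Individuals with SCI (N=196) will be randomized to a WI arm or a WI+JITAI arm". The section also says that the size of the WI+JITAI arm is set by the power needed for the primary aim.

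**The concern.** A dropout allowance should return the required number once the assumed losses are taken away. Here, 20% off 98 does not return 82. The three figures (82 needed, 20% lost, 98 recruited) stand next to each other and cannot all hold.

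What is at stake is the power statement for the primary aim. The 82 per group has no slack, since it gives almost exactly 80%. Any shortfall in completers therefore takes the trial below its stated target on its own assumptions. A reader who accepts the section as written will believe that the trial keeps 80% power for 0.44 after the expected dropout.

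**Working it through.** **Inputs**, all from Sample Size Determination: standardized difference 0.44 (so SD = 1), two-sided α = 0.05, power 80%, 1:1 allocation, dropout 20%, planned 98 per group.

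**Step 1. Reproduce the 82.**

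- Normal approximation: n = 2 × [(1.960 + 0.842)/0.44]² = 81.08, rounded up to 82 per group.
- Two-sample t test: n = 82.05 per group, and power at n = 82 is 0.7997, or 80.0%.

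The stated 82 is sound.

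**Step 2. Apply the dropout.** To keep n after losing a fraction d, recruit n/(1 − d).

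- Per group: 82/(1 − 0.20) = 102.5, so 103 per group and 206 in total.
- Inflating the total directly: 164/0.80 = 205.
- Multiplying by 1 + d instead: 82 × 1.2 = 98.4 per group, or 164 × 1.2 = 196.8 in total.

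The planned 98 and 196 agree with the multiplied version, dropping the fraction, and not with the divided one. The gap is 103 − 98 = 5 per group and 206 − 196 = 10 in total, more than rounding can explain.

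**Step 3. What 98 per group leaves.**

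- 98 × 0.80 = 78.4 per group, so about 78.
- In total, 196 × 0.80 = 156.8, against 2 × 82 = 164 needed.
- The largest dropout that still leaves 82 is 1 − 82/98 = 16.3%.

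**Step 4. Power for 0.44, and the difference detectable with 80% power.**

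| Completers per group | Power, normal approximation | Power, t test | Difference detectable with 80% power (t test) |
|---|---|---|---|
| 82 | 80.4% | 80.0% | 0.440 |
| 78 | 78.5% | 78.0% | 0.451 |

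The normal-approximation power is Φ(0.44 × √(n/2) − 1.960). For n = 78 this is Φ(2.748 − 1.960) = Φ(0.788) = 0.785.

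**Step 5. Secondary aim.** The microrandomized comparison needs 69 in the WI+JITAI arm. With 78 completers it still has them.

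**The case against.** Four points can be made for the plan.

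1. **The effect is small.** The loss is about two points of power, or 0.01 on the standardized scale, which is less than the uncertainty in either the 0.44 or the 20%. Design, randomization and analysis are unaffected. This is true, and it is why the remedy need not involve more participants. It does not make the printed figures agree.

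2. **The 20% may cover the whole 24 weeks, whereas the primary analysis ends at week 16.** Assume, since the article does not say so, that the 20% is a 24-week figure with constant attrition. Loss by week 16 is then 1 − 0.8^(16/24) = 13.8% counted from entry, leaving 84.5 of 98. Counted from randomization after the two-week baseline, it is 1 − 0.8^(14/22) = 13.2%, leaving 85.0. If all losses come before week 16, 78 remain. The range is therefore about 78 to 85 and includes 82. But the section gives the 20% no time horizon and applies it directly to the primary requirement, so this reading has no support in the text.

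3. **The primary analysis uses partial data.** The Primary Aim Analysis section states: "we will fit a mixed-effects model in which the group indicator variable is a predictor", with measurements at weeks 2, 8 and 16. Someone lost after week 8 still contributes, so some information may be recovered. The sample-size section takes no credit for this: it sizes a two-group difference and then adds an explicit allowance for dropout. Week 2 is also the end of baseline, so a participant lost before week 8 has no outcome under treatment in this model.

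4. **The 1.2 multiplier is inferred.** That is correct, because no formula is printed. The contradiction does not depend on it: 98 less 20% is 78.4 by whatever route 98 was obtained.

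Points 1 and 3 limit the practical consequence. None of the four reconciles 82, 20% and 98.

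**Conclusion.** The concern holds. The requirement of 82 is right and the dropout adjustment is wrong as written. On the plan's own inputs, 196 participants leave about 78 per group, with 78.0% power for 0.44 (two-sided t test, α = 0.05), or 80% power for 0.451. Keeping 20% dropout and 80% power for 0.44 would require 206.

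This rests on the simple completer calculation that the section itself uses, in which all of the 20% are lost to the primary comparison and contribute nothing. Realized power under the mixed model could be somewhat higher, but the article gives no basis for a figure. The error is certain and its size is small.

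**What to change.** Keep 196 and correct the statement in Sample Size Determination, for example: *With 20% dropout, 98 participants per group leave about 78 per group, which gives 78% power for a standardized mean difference of 0.44, or 80% power for a difference of 0.45.* This costs one sentence, a slightly less favourable power claim and no extra participants.

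If the sponsor prefers to keep 80% power for 0.44 with 20% dropout, the target becomes 103 per group, 206 in total. That is ten more participants, and the totals in the Abstract, Objectives and sample-size section would all change. The Results section says that enrollment was still open when the article was submitted.

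Lowering the assumed dropout to about 16% so that 98 fits is not a sound repair. The article bases its 20% on prior research and the pilot study and offers nothing in support of a lower figure. If the sponsor means to rely on partial data in the mixed model, or on a 24-week horizon for the 20%, the section should say so and show the resulting power.

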### Recruitment

Our collaborative research team will work with coinvestigators from Magee Rehabilitation Hospital, MossRehab Hospital, Thomas Jefferson University Hospital, and Good Shepherd Rehabilitation Network to recruit participants for this study. We have an established collaboration for the past 6 years. Participants will be recruited through a multipronged approach including (1) the clinicians identifying patients with SCI at their clinics who are eligible for the study and providing them with study flyers, (2) flyers being placed in the common areas of the outpatient clinics, and (3) flyers being distributed through their listserves. In addition, we will send flyers to local and national support groups for individuals with SCI in the United States to increase the visibility of our study.

### Eligibility Criteria

Participants will be included if they (1) are aged 18 to 75 years; (2) have a traumatic (neurological level of injury at cervical level 5 and below) or nontraumatic SCI; (3) are ≥6 months after SCI; (4) use a manual or a power wheelchair as their primary means of mobility (>80% of time); (5) show readiness for PA as assessed by the Physical Activity Readiness Questionnaire; (6) can use their upper arms for exercise; (7) can use a smartphone including interacting, recharging, and carrying it with them; and (8) can use a smartwatch including interacting, recharging, and wearing it. Participants will be excluded if they (1) have any secondary complications such as pressure injuries, contractures, and infections that medically restrict their activity in any way; (2) are diagnosed with traumatic brain injury; and (3) have a history of cardiovascular disease.

### Screening

Participants who contact us and indicate an interest to participate in the study will be informed about the inclusion and exclusion criteria. Participants will verbally indicate if they meet the criteria. If they meet the criteria, we will schedule a first meeting with them. If they do not qualify, we will not record or store any data.

### Protocol and Assessments

#### Participant Meetings

All study procedures will be performed at Temple University or in the community. Our team can work with the participants remotely via Health Insurance Portability and Accountability Act–compliant video conference meeting software, such as Zoom (Zoom Video Communications), to obtain study-related information; we will send participants an Android-based smartphone and a smartwatch through postal mail. The research team can also meet with participants for a 30-minute face-to-face meeting if they prefer and are located within the greater Philadelphia region. All precautions will be taken to minimize the risks to participants and the research staff during the face-to-face meeting. Recruiting individuals who wish to remotely participate in the study will help improve the chances of including individuals with SCI who face transportation barriers, boost recruitment, and enhance retention.

The initial meeting will allow individuals with SCI to provide informed consent and answer questions about their demographics, SCI, wheelchair, and health and activity history. From prior research studies, the investigators estimate that the questionnaires will take approximately 60 to 90 minutes to complete (Textbox 2). Participants will also answer questionnaires 4 to 12 indicated in Textbox 2 at the end of weeks 2, 8, 16, and 24.

Questionnaire answered by the participants at the initial meeting (numbers 1-12) and at the end of weeks 2, 8, 16, and 24 (numbers 4-12).
**Questionnaire**
1. Demographics (eg, age, biological sex, gender, race, ethnicity, and marital status)2. Spinal cord injury (SCI) and level of injury (SCI Core Data Set Form, SCI Spinal Column Injury Basic Data Set Form, Non-traumatic SCI Data Sets Version 1.0 Form, and American Spinal Cord Injury Association Impairment Scale)3. Mobility (Assistive Mobility Devices and Orthoses Form)4. Pressure injuries (Pressure Ulcer Scale for Healing Tool 3.0), if applicable5. Pain (International SCI Pain Basic Data Set Version 2.0 Form)6. Fatigue (Neuro-QOL Item Bank Version 1.0 Fatigue Short Form)7. Function (Spinal Cord Independence Measure III)8. Quality of life (Quality of Life Basic Data Set Version 1.0)9. Physical activity (PA) history (Physical Activity Recall Assessment for people with SCI Survey and Leisure Time Physical Activity Questionnaire for People with SCI Survey)10. PA behavior (SCI Physical Activity Behavior Survey)11. Barriers to PA (Barriers to Physical Activity Questionnaire for People with Mobility Impairments)12. Participants’ motivation (Physical Activity and Leisure Motivation Scale)

#### Allocation and Blinding

After the baseline data collection, participants will be randomly allocated to one of 2 study arms (WI arm or WI+JITAI arm) based on the randomization schedule established by the project biostatistician. Participants will be block randomized on the basis of their level of injury: tetraplegia (higher-level injury) versus other (lower-level injury).

Participants will be masked (single blinding) to the study arm. All participants will receive the same WI program and commercial off-the-shelf technology. Participants in both arms will have access to minutes of moderate-intensity PA performed over the last 7 days, which is designed to motivate them to use the smartwatch in the community. In addition, the participants in the WI+JITAI arm will receive randomized prompts of various types of tailored feedback and PA recommendations over the course of the study.

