### Statistical Analysis

#### Overview

For all aims, descriptive statistics will be obtained to assess distributional assumptions, and any transformations will be applied if needed. In addition, we will examine patterns of missingness and handle this appropriately through either multiple imputation or using models that can appropriately handle missingness (eg, mixed-effects models). We will also examine whether there are any group differences on baseline covariates (eg, pain, fatigue, health, and activity history) despite randomization, and if so, we will statistically control for these variables in our models. All analysis will be performed with an α level of .05.

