#### Exploratory Analysis

Moderators will include age, biological sex, race, ethnicity, level of injury, function, mobility, pain, and fatigue. The exploratory analysis aims to identify subgroups of individuals with SCI who are likely to benefit the most from the integration of just-in-time PA feedback and recommendations with WI. We will conduct 2 moderation analyses. First, we will incorporate moderators into our primary aim models to identify subgroups of individuals with SCI who are likely to benefit the most from the integration of just-in-time PA feedback and recommendations with WI. Second, we will address potential time-varying moderators, such as prior PA and engagement with the JITAI, self-reported pain (number and type), and fatigue, which can be incorporated into the model described in the secondary analysis [52]. Engagement with JITAI will be captured by participants’ response to the “Got it” pop-up button that appears on the smartwatch when they receive a JITAI message. We will also examine potential time-invariant moderators such as biological sex and SCI level. This analysis will allow us to identify subgroups of individuals who are likely to benefit from particular types of messages (eg, tailored vs standard messages).

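### The primary model omits the factor used to block the randomization (level of injury); if that factor predicts change in physical activity, the test is mildly conservative and forgoes a little efficiency

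*Protocol article*

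**What the plan says.** Four places in the protocol article bear on this.

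- **Allocation and Blinding:** "Participants will be block randomized on the basis of their level of injury: tetraplegia (higher-level injury) versus other (lower-level injury").
- **Primary Aim Analysis:** "we will fit a mixed-effects model in which the group indicator variable is a predictor". The activity data analysed are those from weeks 2, 8 and 16. The section goes on: "We will include an interaction with time in the model because we hypothesize that although PA levels may increase in both groups", with a larger rise expected in the arm that receives the just-in-time component. Finally: "We will also include a random intercept and slope for time". Level of injury is not named. Week 24 is added to the same model for the longer-term question.
- **Statistical Analysis, Overview:** baseline covariates are to be compared between the arms, "despite randomization, and if so, we will statistically control for these variables in our models". This is the only stated route by which a covariate reaches the main models.
- **Exploratory Analysis:** "Moderators will include age, biological sex, race, ethnicity, level of injury, function, mobility, pain, and fatigue". These are to be added to the primary aim models afterwards, which suggests that those models do not already contain level of injury.

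**The concern.** When allocation is balanced within levels of a prognostic factor, the design removes that factor's contribution from the comparison between arms. A model that ignores the factor still counts its variance as error. The reported standard error then exceeds the true one, the test rejects too rarely under the null, and some available power is not used.

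The covariate rule makes this worse than simple silence. It admits a variable when the arms differ on it, and blocking on level of injury is meant to prevent exactly that. The factor singled out for control at randomization is thus the one the rule is least likely to let into the analysis.

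There is some reason to think the factor matters for activity in general. The section on personalized thresholds says that deficits at different neurological levels produce large differences in upper-limb use. What is at stake is efficiency, not validity.

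**Working it through.** **1. Reproduce the plan's own figure.** Inputs from Sample Size Determination: standardized difference d = 0.44, two-sided alpha 0.05, power 80%. Per group, n = 2 × (1.960 + 0.842)² / 0.44² = 81.1, which rounds up to 82. The t-test version gives 82.05. The stated 82 reproduces. The calculation is a plain two-group comparison and takes no credit for blocking or covariate adjustment.

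**2. Numbers expected to be evaluable.** 98 per group less the anticipated 20% dropout: 98 × 0.80 = 78.4, so about 78 per arm. With the factor having no effect, power is Φ(0.44/√(2/78) − 1.960) = Φ(2.748 − 1.960) = 78.5% by the normal approximation (78.0% by the t-test).

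**3. Effect of ignoring the factor, for a given strength.** Let R² be the share of the variance of the analysed contrast that level of injury explains. The article gives no value; 0.05 to 0.15 is assumed. With allocation balanced within levels, the true standard error is √(1 − R²) times the one the unadjusted model reports. Hence:

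- type I error, unadjusted = 2 × [1 − Φ(1.960/√(1 − R²))]
- power, unadjusted = Φ((2.748 − 1.960)/√(1 − R²))
- power, adjusted = Φ(2.748/√(1 − R²) − 1.960)

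| R² (assumed) | Type I error, unadjusted | Power, unadjusted | Power, adjusted | Gain (points, before rounding) |
|---|---|---|---|---|
| 0.05 | 4.4% | 79.1% | 80.5% | 1.4 |
| 0.10 | 3.9% | 79.7% | 82.5% | 2.9 |
| 0.15 | 3.4% | 80.4% | 84.6% | 4.3 |

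Unadjusted power rises with R² because blocking reduces the true variance whether or not the model uses the factor.

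**4. What this means for the contrast actually tested.** The primary contrast is group by time, so R² in step 3 refers to change in activity, not its level. The planned model was simulated with measurements at weeks 2, 8 and 16, allocation balanced within injury level, and a random intercept and slope. The variances were assumed: intercept 1.0, slope 0.5 over the 14 weeks, residual 0.4. There were 150 replicates without dropout (82 per arm) and 90 with 20% dropout (98 per arm). Mean standard error of group by time:

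| Scenario | Without level | + level | + level × time |
|---|---|---|---|
| Level explains 20% of intercept variance, no dropout | 0.1767 | 0.1767 | 0.1767 |
| Same, 20% dropout | 0.1787 | 0.1786 | 0.1787 |
| Level also explains 10% of slope variance, 20% dropout | 0.1789 | 0.1782 | 0.1743 |

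A constant difference between injury levels leaves the standard error practically unchanged. A gain appears only when level predicts the slope and its interaction with time is fitted: 1 − 0.1743/0.1789 = 2.6%. Because the variances are assumed, only the comparison across columns is informative.

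**5. Linking steps 3 and 4.** With complete data and time scaled as 0, 6/14 and 1, the sum of squares about the mean is 0.503. The variance of one participant's slope is then 0.5 + 0.4/0.503 = 1.295. Ten percent of the slope variance is 0.05, and 0.05/1.295 is an R² of about 0.04. To reach R² of 0.05 to 0.15 under these assumed variances, level would have to explain about 13% to 39% of the true slope variance (0.05 × 1.295/0.5 and 0.15 × 1.295/0.5). The upper end of the table in step 3 is therefore demanding.

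**The case against.** The strongest reply is that this is a condensed article. Group is called a predictor, not the only one; the covariates in the overview are examples; and a full covariate list may sit in an analysis plan that is not shown. That would dispose of a complaint about mere omission. It does not dispose of this one, because the article states a rule for covariate entry, and that rule works against the factor used in the design.

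A second reply is that nothing in the article says level of injury predicts change in activity. Moderate-intensity minutes are scored against a threshold set for each participant, precisely because deficits vary by neurological level, and this may weaken the link. This stands, and it is why the consequence can only be stated conditionally.

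Three stronger readings are tempting, and the document supports none of them:

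- A reader might infer that the standard errors are simply too large and power is lost. For group by time with a random intercept, that needs level of injury to predict change, not merely the amount of activity.
- A reader might compare roughly 78% power without adjustment against 80% to 85% with it. The 78% figure assumes the factor explains nothing, so the two sides rest on different assumptions. The like-for-like gain is the one in the table.
- A reader might conclude that the planned 80% is eroded by this choice. The sample size never assumed adjustment. The shortfall to 78 per arm comes from the dropout allowance (82/0.80 would be 103 per group, not 98), which is a separate matter.

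**Conclusion.** The mismatch between design and analysis is in the stated plan: randomization is blocked by level of injury, the described primary model leaves the factor out, and the adjust-if-imbalanced rule is unlikely to bring it back. Any error is in the conservative direction, with no bias and no inflation of false positives. The type I errors of 4.4% to 3.4% and the gains of about 1.4 to 4.3 power points at 78 per arm rest on the assumed 5% to 15% of contrast variance. If level of injury has no bearing on change in activity, the loss is practically nil. It is a minor efficiency point and a free improvement.

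**What to change.** State in the primary aim analysis that level of injury (tetraplegia versus other, as used in the blocking) and its interaction with time are fixed terms in the primary model and in the model extended to week 24, whatever balance is observed at baseline. The interaction is the part that matters, since a main effect alone hardly touches the group-by-time contrast. Level of injury can still be examined as a moderator in the exploratory analysis, through its three-way interaction with group and time.

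The cost is one sentence and a few degrees of freedom. In the simulated scenarios the added terms did not raise the standard error appreciably even where there was nothing to gain.
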